#### **2.1.1 Cohort 1**

All patients will contribute to the analysis based on the total number recruited.

The primary outcome measure is the number of patients with severe or very severe treated skin site reactions as determined by modified Draize score (See Appendix A)

Patient perception of treatment is a secondary outcome measure as measured by the patient treatment questionnaire (See appendix B). Positive patient perception will be reported descriptively as a proportion of the number of patients recruited.

Statistical analysis for all outcome measures will be exploratory based on descriptive data. Continuous measurements (including QoL measures) will be summarised and reported as medians and ranges (inter-quartile ranges). Categorical data (including proportions of patients with positive patient perception and with adverse events) will be summarised and reported as percentages and confidence intervals (95%).

QoL tools (EQ5D, DLQ) will be scored according to scoring manuals and actual scores will be reported descriptively.

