#### **2.1.2 Cohort 2**

All tumours will contribute to the analysis based on the total number randomised (intention to treat population). A secondary analysis will be reported based on the number of tumours which have been treated for 12 weeks (per protocol population).

The primary outcome measure is the number of tumours responding to treatment by 12 weeks reported as a proportion of the number of tumours randomised in the actively and placebo groups separately.

According to WHO-RECIST criteria, a reduction in 30% volume would be sufficient to classify a 'response' to treatment in oncology. In this trial we will use this criteria as a bench mark when determining a response in this patient population. As such one of the outcomes will be to consider and confirm a definition of 'response' to treatment in this group of patients. Tumour volume will be measured on 8 - 10 predetermined identified tumours in each patient prior to randomisation (baseline) and measured again on the same tumours at 4 and 12 weeks. The change in volume for each tumour will be recorded and classified as either having a response to treatment or not.

As an early phase trial, statistical analysis will be exploratory (not based on hypothesis testing) and will be based on descriptive data presented by treatment group. Continuous measurements (including change in tumour volume from baseline) will be summarised and reported as medians and ranges (inter-quartile ranges). Categorical data (including proportions of tumours with adverse events and outcomes from the Pain Assessment Forms) will be summarised and reported as percentages and confidence intervals (95%). Since multiple tumours are sited in individual patients, a secondary analysis based on a multi-level

modelling approach will be undertaken to investigate the relationship between any change in volume and randomised treatment accounting for the multi-level nature of the tumour measurements.

QoL tools (EQ5D, DLQ) will be scored according to scoring manuals and actual scores will be reported descriptively.

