In cohort 1, participants who withdraw from trial drug prior to visit 3 will still be followed up and included in analysis, if they are happy to do so, but additional participants may be recruited provided withdrawal is not related to safety issues.

In cohort 2, participants who withdraw from trial drug will still be followed up and included in analysis, if they are happy to do so, but additional participants may be recruited and randomised as not to affect the recruitment target of 150 tumours and provided withdrawal is not related to safety issues.

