## **5. STUDY POPULATION**

### **5.1 Defining Populations for Analysis**

All patients recruited to Phase 1b will be known as the Phase 1b trial set and to 2a the Phase 2a trial set, as intention to treat sets.

All eligible patients/tumours who start treatment in phase 1b will be known as the Phase 1b treatment set and in Phase 2a the Phase 2a treatment set.

All eligible patients/ tumours who start and complete 12-weeks of treatment in phase 2a will be known as the Phase2a protocol set. If further subsets emerge they will be named appropriately.

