## **6. TREATMENT RECEIVED**

Phase 1b will be open label and Phase 2a will be a randomised double blind trial.

In both Phases the dose will be one application in the evening to each tumour as directed at the first visit by the research nurse/doctor. Application will be recorded in a patient diary.

In Phase 1b the participant's will treat their selected tumour with the active treatment for a 4 week period. In Phase 2a all participants will be treating tumours on one half of the body with active CT327 and the other half of the body with placebo according to the randomisation allocation for a 12 week period.

Withdrawals from treatment are cases where the trial drug is discontinued. This may be because the participant decides they no longer wish to continue, cessation of the trial drug is

recommended by the investigator, the participant is pregnant, there is a significant medical condition or an adverse localised or systemic reaction. In both cohorts, participants who withdraw from trial drug prior to the end of treatment visit, will be followed up and included in the analysis, if they are happy to do so.

The analysis sets are the Phase 1b treatment set and the Phase 2a treatment set.

Compliance to the treatment will be reported (Appendix 2) at the patient level as the percentage compliance in terms of days of missed ointment for all tumours. If additionally individual tumours have had missed treatment this will be reported at the tumour level as the number of missed applications (in days) as reported in the diary cards. The total number of applications, at the tumour-level, will be also be reported as median days (IQR, range), over 4 weeks in Phase 1b and over 12 weeks in Phase 2a.

The expected number of applications in a 4-week (28 day) period is 28 and in a 12 week (84 day) period is 84 (+/-3 days dependent on EoT visit date). Compliance to treatment will be summarised as the number of days on treatment (date end-date start) as recorded in the patient diary and reported as median (IQR, Range), as well as the proportion of protocol treatment received, calculated as the number of days of applications as a proportion of the 28/84 day protocol treatment, and reported with 95% Confidence Interval (CI).

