#### **8.2.2.2 Primary Analysis of Response**

The number of tumours classified as responding to treatment will be reported as a proportion of the trial set with 95%CI at 12 weeks by randomised treatment group. Response to treatment

is classified according to the WHO-RECIST criteria, where a response is either a complete response (disappearance of tumour) or a partial response (decrease in tumour volume of  $\geq 30\%$  at 12 weeks). Non-response is either stable disease (neither complete nor partial criteria met), or progressive disease (increase in tumour volume with no complete response, partial response or stable response reported before increase).

A sensitivity analysis of the Phase 2a primary outcome of response rate will be carried out on the Phase2a 'per protocol' set.

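### Protocol 15.2 and SAP 6 make inclusion in the analysis, not only further follow-up, depend on the willingness of a participant who stops trial drug, which conflicts with the all-recruited and all-randomised analysis sets

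*Combined protocol and SAP*

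**What the plan says.** **Conditional statements.** In Protocol 15.2, cohort 1 participants who stop trial drug "prior to visit 3 will still be followed up and included in analysis, if they are happy to do so". The matching sentence for the second cohort reads "In cohort 2, participants who withdraw from trial drug will still be followed up and included in analysis, if they are happy to do so". SAP 6 covers both cohorts: those who stop before the end-of-treatment visit "will be followed up and included in the analysis, if they are happy to do so".

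**Unconditional statements.** For cohort 1, Protocol 14.1 (sub-heading 2.1.1) says "All patients will contribute to the analysis based on the total number recruited". For cohort 2 (sub-heading 2.1.2) it says "All tumours will contribute to the analysis based on the total number randomised (intention to treat population". SAP 5.1 defines everyone recruited to each phase as "known as the Phase 1b trial set and to 2a the Phase 2a trial set, as intention to treat sets". SAP 8.2.1 reports the Phase 1b primary outcome in the trial set. For Phase 2a, SAP 8.2.2.2 says "The number of tumours classified as responding to treatment will be reported as a proportion of the trial set with 95%CI at 12 weeks".

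**Related rules.** Under Protocol 15.2, a modified Draize score of 4 or above leads to discontinuation. The same cut-off defines the cohort 1 primary event. SAP 8.1.1 takes the score at the end of treatment, and the cohort 1 outcome table in Protocol section 7.1 places it after 4 weeks. Protocol 15.2 also allows extra participants to be recruited, unless the withdrawal was for safety.

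**The concern.** Whether to attend more visits is rightly the participant's choice. Membership of an intention-to-treat set is not, because it is fixed at recruitment or randomisation. Joining the two under one condition gives an analyst a written basis for leaving out someone who stops the ointment and declines further visits. No section says which rule prevails, and SAP 6 and SAP 5.1 disagree within one document.

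Those who stop and decline are unlikely to be a random subset. Local reactions, the burden of treatment and lack of visible effect are all plausible reasons. Leaving them out would tend to lower the reported reaction rate and raise the reported response rate. In cohort 1 the link is direct, because the event that stops treatment is also the primary event.

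**Working it through.** **1. The two rules for the same person.** Take a recruited participant who stops the drug and declines further visits.

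| Source | In the analysis? |
|---|---|
| Protocol 15.2, SAP 6 | Promised only if willing |
| Protocol 14.1, SAP 5.1, 8.2.1, 8.2.2.2 | Yes, no condition |

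Earlier in Protocol 15.2, permission for follow-up data and willingness to give end-of-trial data are already dealt with separately. The later sentence attaches the condition to inclusion as well.

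**2. Missing outcomes.** No section states how to count a recruited patient without an end-of-treatment Draize score, or a randomised tumour without a 12-week volume. The response table in SAP Appendix 3 has no row for tumours not assessed. The table in Appendix 4 has a column headed as not applicable, with no definition.

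**3. Cohort 1, n = 8 (Protocol 14.2).** Exact (Clopper-Pearson) limits. Suppose one patient has a severe reaction, stops, and declines further visits.
- Counted: 1/8 = 12.5%. The lower limit is 1 − 0.975^(1/8) = 0.3%. The upper limit is the 97.5% point of Beta(2, 7) = 52.7%.
- Patient left out: 0/7 = 0%. The upper limit is 1 − 0.025^(1/7) = 41.0%.
- Patient kept, but the event not counted because there is no end-of-treatment score: 0/8 = 0%. The upper limit is 1 − 0.025^(1/8) = 36.9%.

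The third case shows that restoring the denominator alone is not enough. The timing of the score also needs a rule.

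**4. Cohort 2: the plan's own design first.** Inputs from Protocol 14.2 are 75 active tumours, p0 = 5%, p1 = 15%, type I error 3.4% and type II error 10.8%. The critical number r is held in a separate document. From the exact binomial:
- r = 8: P(X ≥ 8 | 75, 0.05) = 0.0336 and P(X ≤ 7 | 75, 0.15) = 0.1082. Both match the stated errors.
- r = 7 gives a type I error of 8.1%, and r = 9 gives a type II error of 18.9%. Only 8 fits, so 8 is inferred here.

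**5. Cohort 2: effect of exclusion.** Assume two patients with 5 active tumours each (the plan allows 4 or 5 per side), none responding, are left out and not replaced: 75 − 2 × 5 = 65.
- All randomised: 8/75 = 10.7% (95% CI 4.7 to 19.9%).
- After exclusion: 8/65 = 12.3% (5.5 to 22.8%).

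These intervals treat tumours as independent. The responder count is 8 either way. Each patient also contributes placebo tumours. With 5 on that side too and none responding, any placebo rate is multiplied by the same 75/65 = 1.15.

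**The case against.** The strongest reply is that the willingness clause concerns attendance, which is what a participant does. Nothing says that declining removes a patient or discards data already collected. The definitions that name the primary analysis populations are unconditional, and SAP 3.3 keeps even ineligible patients in the intention-to-treat analysis. The sentence in SAP 6 sits in a section on treatment received, whose stated set is the treatment set. SAP 7 reports adverse events from the start of treatment with no completion condition. A reported site reaction is assessed in clinic, so a score should exist before any refusal. Read literally, the trial-set denominator in SAP 8.2.2.2 already treats an unmeasured tumour as not responding.

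Most of this stands, and it is why the loss is possible rather than certain. It does not remove the conflict, because the sentence names inclusion in the analysis and no section ranks the two rules.

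Three stronger readings are tempting, and the documents do not support them.
- **That cohort 1 progression could be reached by exclusion, with four events read as three.** Protocol 14.3 counts patients who experienced events, not members of an analysis set, so a recorded event would have to be ignored. The version in Protocol 6.1 needs at least 5 of 8 patients at a score of 3 or below. With four events only 4 qualify, whoever is left out.
- **That the Phase 2a decision would change.** The critical number is compared with a count of responders, and removing non-responders leaves that count alone.
- **That the wording inflates the type I error.** Suppose 1, 2, 3 or 4 patients with 5 active tumours each are replaced, giving 80, 85, 90 or 95 active tumours, and r stays at 8. Then P(X ≥ 8 | N, 0.05) is 4.7%, 6.2%, 8.1% or 10.3%. These figures are the same if every non-responder is kept. They come from recruiting beyond 75 against a fixed critical number, not from this sentence.

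**Conclusion.** The plan states two incompatible rules for participants who stop trial drug, and one of them permits outcome-related exclusion from a set labelled intention to treat. Whether anyone would be lost depends on which section the analyst follows. If the SAP trial sets and SAP 7 govern, these participants and their adverse events stay in.

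The consequence is largest in cohort 1, where one person can move the primary result from 12.5% to 0%. In cohort 2 it is limited to the reported rates, about 1.6 percentage points (12.3 − 10.7) in the example, with the placebo side affected too. The documents give no withdrawal rate, so one patient in cohort 1 and two in cohort 2 are illustrations, not forecasts. The 5 tumours per side and the critical number of 8 are likewise an assumption and an inference. The point should be corrected before analysis, as a repair to the wording rather than a flaw in the design.

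**What to change.** - **Protocol 15.2 (both cohorts) and SAP 6:** state that only further follow-up depends on the participant's agreement. All participants who stop drug stay in the SAP 5.1 trial sets. Data collected up to the point of declining follow-up are analysed, subject to the consent given (the consent form is not in the copy reviewed).
- **SAP 8.1.1:** state that a modified Draize score of 4 or above recorded at any time on treatment, including one that leads to discontinuation, counts in the cohort 1 primary outcome. Align the cohort 1 outcome table in Protocol section 7.1 with this.
- **SAP 8.2.2.2:** state that a randomised tumour without a 12-week volume counts as a non-responder in the trial-set analysis, and give such tumours their own row in the Appendix 3 table.

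The cost is a few sentences in each document and no new data collection. Reported reaction rates may be slightly higher and response rates slightly lower. The participant's right to decline visits is unchanged.

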## **16. Data monitoring, quality control and quality assurance**

The trial may be prematurely discontinued on the basis of new safety information, or for other reasons given by the Data Monitoring Committee and/or Trial Steering Committee, Sponsor, regulatory authority or ethics committee concerned.

The trial will be managed through NCTU. The Chief Investigator [name] will be responsible for the day-to-day trial conduct at site.

NCTU will provide day-to-day support for the site and provide training through Investigator meetings, site initiation visit and routine monitoring visits.

Quality control will be maintained through adherence to NCTU SOPs, trial protocol, Statistical Analysis Plan (SAP), the principles of GCP, research governance and clinical trial regulations.

An independent data monitoring committee (DMC) (2 physicians not connected to the trial, one statistician) will be convened to undertake independent review. The purpose of this committee will be to monitor safety in cohort 1 and recruitment, safety and outcomes in cohort 2. The DMC may request access to unblinded trial data. The DMC will meet at least 3 times; at the start, following completion of cohort 1 data collection and following completion of cohort 2 data completion. At the first meeting, DMC will agree meeting timelines and discuss stopping guidelines.

A Trial Steering Committee (TSC) will be established to provide overall supervision of the trial. The TSC will consist of independent chair, further independent clinician, independent consumer representative, funder representative & Trial Management Group. The committee will meet before the start of the trial to approve the protocol and at least annually thereafter for the duration of the trial. The Chair of the TSC and the PI can request meetings more frequently if needed and if also requested by the DMC.

### **16.1 Data Monitoring**

Monitoring of trial conduct and data collected will be performed by a combination of central review and site monitoring visits to ensure the trial is conducted in accordance with GCP. Trial site monitoring will be undertaken by NCTU. The main areas of focus will include consent, serious adverse events, essential documents in trial files and drug accountability & management.

Site monitoring will include:

- All original consent forms will be reviewed as part of the site file. The presence of a copy in the patient hospital notes will be confirmed for 100% participants

- All original consent forms will be compared against the trial participant identification lists
- All reported serious adverse events will be verified against treatment notes/medical records (source data verification)
- The presence of essential documents in the investigator site file and site files will be checked
- Source data verification of primary endpoint data and eligibility data for 100% of participants entered in the trial cohort 1 and 50 % of participants in trial cohort 2.
- Drug accountability and management will be checked

Central monitoring will include:

- All applications for trial authorisations and submissions of progress/safety reports will be reviewed for accuracy and completeness, prior to submission
- All documentation essential for trial initiation will be reviewed prior to site authorisation

All monitoring findings will be reported and followed up with the appropriate persons in a timely manner.

The trial may be subject to inspection and audit by Newcastle Upon Tyne Hospitals NHS Foundation Trust (NUTH) under their remit as sponsor, and other regulatory bodies to ensure adherence to GCP. The investigator(s) / institutions will permit trial-related monitoring, audits, REC review and regulatory inspection(s), providing direct access to source data/documents.

## **16.2 Discontinuation rules**

The trial may be prematurely discontinued on the basis of new safety information, or for other reasons given by the Data Monitoring Committee and/or Trial Steering Committee, Sponsor, regulatory authority or ethics committee concerned.

If the trial is prematurely discontinued, active participants will be informed and no further participant data will be collected.

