## ***Week 2 - Telephone call***

- Patients will be contacted via telephone after 2 weeks to ask if they are managing the administration of the ointment and if they have any concerns or questions.

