## ***Week 6- Telephone call***

- Patients will be contacted via telephone after 6 weeks to ask if they are still managing the administration of the ointment and if they have any concerns or questions.

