### ***Telephone call (4 week follow up)***

Participants will be contacted by telephone 4 weeks after completing the trial to ensure there have been no further significant adverse events during this period. They will be asked if they have experienced any treatment site reactions since stopping treatment, or any other side effects. If necessary an appointment will be made for the participant to have a follow up visit in clinic for assessment and management.

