| Trial medication dispensed               |                          |                                                                                |   | X |                | X                                       |                |                           |                      |
| Trial medication returned                |                          |                                                                                |   |   |                | X                                       |                | X                         |                      |
| Patient Diary                            |                          |                                                                                |   | X |                | X                                       |                | X                         |                      |

|                         |  |  |   |   |  |   |  |   |   |
|-------------------------|--|--|---|---|--|---|--|---|---|
| Lesions biopsied        |  |  |   |   |  |   |  | X |   |
| Adverse events          |  |  |   |   |  | X |  | X | X |
| Concomitant medications |  |  | X |   |  | X |  | X |   |
| CRF completion          |  |  |   | X |  | X |  | X | X |

 Patient information sheet can be post to avoid any unnecessary journey

 A minimum of 24hr for review of patient information sheet before patient can sign informed consent form

 QoL only to be completed if patient was not part of the cohort 1 trial.

 Pregnancy test should be urine dipstick and for all women of childbearing potential.

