### 17.3 Protocol Specifications

For purposes of this protocol:

- All non-serious adverse reactions will be recorded at all trial visits
- Any serious adverse events will be recorded throughout the duration of the trial until the final trial visit.
- Serious adverse events exclude any pre-planned hospitalisations (e.g. elective surgery) not associated with clinical deterioration.
- Serious adverse events exclude routine treatment or monitoring of the studied indication, not associated with any deterioration in condition.
- Serious adverse events exclude elective or scheduled treatment for pre-existing conditions that did not worsen during the trial.
- Serious adverse events exclude increases in tumour size [primary outcome measure, already documented and monitored within trial]

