## 17.5 Pregnancies

If a female participant does become pregnant while participating in the trial, trial drug will be discontinued immediately. Details of the pregnancy should be reported to NCTU within 24 hours of learning of its occurrence. The pregnancy must be followed up to determine outcome. Additional follow-up will no longer be required once the newborn is determined to be healthy.

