## **7. SAFETY ANALYSIS**

Most adverse events (AE) and adverse drug reactions that occur in this trial, whether they are serious or not, will be expected treatment-related toxicities due to the drugs used in this trial. For a full list of expected undesirable effects of CT327, please refer to the Investigator Brochure.

AE's are recorded by the clinical staff directly to the database on a three-point scale of severity (mild, moderate or severe) and also by causality (relationship to treatment categorised on a six point scale), as described in the protocol.

The analysis sets are the Phase 1b treatment set and the Phase 2a treatment set.

Any adverse events/reactions from start of treatment and up to the time of tumour excision (Phase 1b) or 4 weeks after end of treatment (Phase 2a), will be categorised according to severity and causality and recorded on the database.

The number of patients (Phase 1b) and tumours (Phase 2a) reporting any AE will be reported clarifying those deemed to be treatment related (Appendix 2).

In Phase 2a, the number of tumours with at least one AE will be reported as a proportion of the total number of tumours. The number of tumours with at least one treatment-related AE, that is those described as definitely, probably or possibly related, will be reported as a proportion of the total number of tumours. The number of tumours with at least one 'moderate' or 'severe' treatment-related AE will be reported as a proportion of the total number of tumours.

The unique number of patients experiencing at least one 'moderate' or 'severe' treatment-related AE will be reported as a proportion of the treatment set.

Proportions will be presented as % (95% CI).

Descriptions of the adverse events may require listing in the text.

No significance testing will be carried out.

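### Protocol 16.2 ends all participant data collection on early discontinuation, even for safety, and so cuts short the SAP 7 adverse event window in cohort 2

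*Combined protocol and SAP*

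**What the plan says.** **Early stopping.** Protocol 16.2 lists new safety information first among the grounds for discontinuing the trial. Its next sentence says that "active participants will be informed and no further participant data will be collected". The ban is not limited to efficacy data and has no exception.

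**Adverse event window.** SAP 7 counts events from the start of treatment "up to the time of tumour excision (Phase 1b) or 4 weeks after end of treatment (Phase 2a". The analysis sets are the treatment sets, so in cohort 2 every eligible patient or tumour that started treatment is in the denominator.

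**Scheduled capture in cohort 2.** The schedule in protocol 13.8 marks adverse events at week 4, at week 12 and at a closing telephone call. Protocol 13.4 says of that call: "They will be asked if they have experienced any treatment site reactions since stopping treatment". The week 2 call is "to ask if they are managing the administration of the ointment and if they have any concerns or questions". The week 6 call has the same purpose, and 13.8 marks both only as compliance assessments.

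**Safety reporting.** Protocol 17.3 says "All non-serious adverse reactions will be recorded at all trial visits" and takes SAEs up to the final trial visit. Protocol 17.4 puts non-serious events arising on drug on the CRF and requires SAEs on drug to be reported within 24 hours. Protocol 17.5 says of pregnancies: "The pregnancy must be followed up to determine outcome".

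**Individual withdrawal.** For a patient who leaves trial drug, protocol 15.2 and SAP 6 still seek follow-up if the patient agrees. Protocol 15.2 also asks for end-of-trial data at the point of withdrawal.

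**The concern.** If a safety signal stops the trial, the most recently exposed patients hold the evidence that bears most directly on it. Under 16.2 what happens to them next would not enter the trial data. Their SAP 7 window could not be completed, yet they would stay in the denominators of the SAP 7 proportions. Those proportions would then mix complete and truncated observation, and the direction of any bias is unknown.

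The rule is also less protective than the one for a single patient who leaves drug, whose follow-up is still sought. The protocol describes this as the first use of CT327 in CYLD defective tumours. Its background section gives earlier exposure as up to 8 weeks, against 12 weeks here, so late reactions are worth recording.

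**Working it through.** The plan states no figure on this point, so there is none to reproduce. The check has three steps. It is confined to cohort 2, because the cohort 1 window closes at excision, which is planned for the week 4 visit.

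**1. Does any other section restore collection after a trial-wide stop?**

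- 15.2 and SAP 6 deal with withdrawal from trial drug. Neither addresses a stop of the whole trial, which 16.2 does expressly.
- 17.3 runs SAE recording to the final trial visit and does not say what happens on an early stop.
- 17.4 covers events during drug treatment, so it does not reach the 4 weeks afterwards.
- The closing call is 4 weeks after visit 4 in the 13.8 schedule, and 4 weeks after trial completion in the 13.4 text. Whether a patient stopped early would get it is unclear.

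None of these clearly overrides 16.2.

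**2. Window lost per patient.** SAP 7 gives 4 weeks = 28 days after end of treatment. Let d be the days from last application to the stop, with d = 0 for a patient on drug.

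Post-treatment days lost = max(0, 28 - d)

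| d (days) | Days lost |
|---|---|
| 0 (on drug) | 28 |
| 7 | 21 |
| 14 | 14 |
| 21 | 7 |
| 28 or more | 0 |

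For a patient stopped mid-treatment there is a second gap. Events since the last visit that have not yet been reported have no end-of-treatment check at which to be picked up. The documents do not allow this part to be sized.

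**3. How many patients could be affected?** A patient is exposed to the problem for 12 + 4 = 16 weeks from starting treatment (visit windows of 3 days ignored). The documents state no accrual period, but SAP 2 gives milestones that bound it under assumptions:

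- Start of accrual (assumed): between 29 May 2015, the Phase 1b DMC date, and 26 August 2015, the date of the protocol version that the SAP cites.
- End point (assumed): 1 November 2016, from the anticipated November 2016 final analysis.
- Last entry (assumed): 4 to 16 weeks before that. SAP 2 requires at least 4 weeks of follow-up; 16 weeks allows full treatment and the call.
- Patients: 15 to 20.

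Longest accrual: 522 days - 28 = 494 days = 70.6 weeks. 
Shortest accrual: 433 days - 112 = 321 days = 45.9 weeks.

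Patients within 16 weeks of starting = N x 16 / accrual weeks, with even accrual:

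- Low: 15 x 16 / 70.6 = 3.4
- High: 20 x 16 / 45.9 = 7.0

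That is roughly 3 to 7 patients at a given time once accrual is under way.

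**The case against.** The best case against the point is that 16.2 sits in the data monitoring section, while pharmacovigilance has its own section 17. Conduct is bound to GCP, unit SOPs and the trial regulations. Investigators must report all SAEs and provide care. The DMC is to discuss stopping guidelines at its first meeting, and these may cover follow-up after a stop; they are not among the documents. The situation arises only if the whole trial stops, SAP 2 sets no statistical stopping criteria, and earlier tolerability was good.

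Much of this stands. It makes the point contingent, and it means that clinical care and events already reported are not at risk. It does not remove the conflict: sites are told to comply with the protocol, and after a stop 16.2 is the sentence they would consult.

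Three stronger readings are tempting, and the documents do not support them:

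- **That all time since the last scheduled adverse event assessment is lost.** Section 17.4 puts events during treatment on the CRF without limiting this to visits. Patients have a contact number, and reported site reactions are reviewed in clinic. Unscheduled is not the same as uncaptured.
- **That patients stopped before visit 4 are excluded from the closing call.** The 13.4 text times the call from completing the trial, and 15.2 shows that visit 4 data can be taken early after withdrawal. The position is unclear, not settled against them.
- **That pregnancy follow-up ends.** Section 17.5 is an unconditional duty, and 16.2 does not clearly displace it.

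It is also fair to say that part of the post-treatment SAE gap comes from the limits in 17.3 and 17.4 themselves, not from 16.2.

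**Conclusion.** The point holds as a conflict between two written rules. Protocol 16.2, taken as written, prevents completion of the SAP 7 adverse event window in cohort 2 after an early stop, including one made for safety. The supportable size is at most 28 post-stop days per affected patient, falling to zero at 28 days off drug, plus a missing check for unreported events in patients stopped mid-treatment.

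The figure of roughly 3 to 7 patients rests on even accrual and the assumed dates above; uneven accrual would move it either way. The number of events lost cannot be estimated, because rates from earlier studies may not apply when a new signal causes the stop. The primary outcome definition and the decision rule are not affected. The amendment should be made because it is cheap and the lost data might not be recoverable afterwards.

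**What to change.** Amend protocol 16.2 to say that early discontinuation ends recruitment, treatment and efficacy data collection, and that the following continue with the patient's agreement:

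- an adverse event check at the stop for cohort 2 patients still on drug;
- AE and SAE collection to 4 weeks after last application in cohort 2, using the existing telephone call timed from last application.

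Add that section 17 duties continue, including pregnancy follow-up under 17.5, and that the SAE limits in 17.3 and 17.4 do not shorten this window. If those limits are also thought too short for patients who complete normally, that is a separate edit to section 17.

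The cost is a short protocol edit. Only if the trial stops early is there more: one re-timed call, a brief check for those still on drug, and minor CRF work per affected patient.
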